### Control group (standard physiotherapy)

The standard physiotherapy group, like the intervention groups, will involve the same number of sessions (24), duration (60 min) and frequency per week (3) of therapy. Standard physiotherapy will comprise one-to-one therapist/patient sessions engaging in impairment-centred mobilisation techniques, standing balance (using varying methods) and functional activities for both upper and lower extremities. All the activities for the control group will be implemented by regular therapists (who are similar in qualification/experience to therapist implementing the CCT programme) in the Physiotherapy Department of AKTH.

### Data analysis

Data will be recorded in Microsoft Excel before being exported to Statistical Package for Social Science (SPSS). Both descriptive and inferential statistics will be used to examine the outcomes of the study.

Descriptive statistics of frequencies, percentages, mean, and standard deviation will all be used to describe baseline assessments and demographic characteristics of participants. Where appropriate, they will also be used at post-intervention and follow-up to describe relevant findings.

Between-groups relative mean differences of the dependent variables, (spasticity, muscle strength, functional independence, ADL, functional capacity, gait speed, upper extremity function and impairment) will be determined using the general linear model repeated measures, MANCOVA models (for each study domain, adjusted central on baseline as covariates). If the MANCOVA is found to be significant (Roy’s largest root), univariate between-groups results will be reported and pair-wise post hoc analysis will be performed using least significant difference.

A multiple regression analysis will be performed to investigate the relation between improvement at different time periods of CCT and performance in each of the specific dependent variables, to detect which of the durations most effectively predicts improvement in such a variable.

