### Participants

Participants will include all stroke survivors in AKTH referred for physiotherapy by consulting physicians. However, only participants who meet the inclusion criteria will be considered for randomisation into the study groups (involving intervention and control groups). Participants will be considered eligible if: stroke is ascertained to be due to cerebrovascular accident; leading to unilateral motor deficits [14]; they provide a written informed consent; they are adult stroke survivors of ≥18 years of age; onset of stroke is ≥30 days; they possess sufficient cognition to participate (having a score of ≥24 points on mini-mental state examination); they are willing to participate in an 8-week intensive CCT programme; have the ability to walk for 10 m unsupported (walking aid is allowed); and have a minimum active wrist extension (2/5 on manual muscle testing). Participants will be considered ineligible if they present with precluding medical comorbidity to exercise, and history of any major surgical procedure significant enough to interfere with performance (general or orthopaedic) in an exercise therapy intervention.

Stroke survivors who meet the eligibility criteria will be randomised into one of four arms of the study, including three intervention categories (60 min CCT, 90 min CCT and 120 min CCT) and one control (60 min standard physiotherapy).

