### Sample size and power calculation

Using power calculations to detect a between-group difference of 42.5 m (0.43 effect size) for a 4-group repeated measure MANOVA in walking distance with 90 % power at α = 0.05, a total sample size of 56 was generated, using an estimated standard deviation (SD) for the calculation as adopted from a meta-analysis [9]. The 42.3 m was proposed as the minimum clinically important difference in walking distance, based on previous studies of implicit measurement error following repeated measurement of speed. The generated total sample size of 56, by implication, will give 14 participants as samples for each group. To incorporate drop-out to follow-up, we hope to recruit a total of 68 participants (17 participants per group). The power calculation was conducted using G*Power version 3.0.10.

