### Procedures

This study has been approved by both the Senate Research Grants and Study Leave Committee University of the Western Cape (South Africa) (ethics number 13/9/33) and the Human Research Ethics Committee of Aminu Kano Teaching Hospital (Nigeria) (NHREC/21/082008/AKTH/EC/1232).

Assessment of participants will be conducted at three stages (baseline, post-intervention, and at 6-months follow-up). To ensure a comprehensive assessment, we chose a battery of measures covering the WHO-ICF model [36]. We selected certain tools to cover the three key domains proposed by the ICF: body structures and function, activity and participation. At baseline, participants will be assessed for socio-demographic characteristics which will include personal demographic information and stroke-specific information. The personal demographic information will include age, sex, height, weight, marital status (pre- and post-stroke), educational qualification, employment (pre- and post-stroke), and tribe. The stroke-specific information will include time since stroke, type of stroke, hemispheric side of lesion, and use of cane. This will be followed by ICF-based assessments, all at baseline. The outcome measures to be employed for these assessments and their function/application are presented in Table 1.

**Table 1 Tab1:** Study assessment tools

Scales	Function/application
Body structure and function assessment	
i. Modified Tardieu Scale (MTS)	
	The MTS measures spasticity [39]. Descriptively, the MTS has two measurements, the quality of muscle reaction (ordinal scale) and the angle of reaction or angle of catch (ratio). The quality of muscle is scored from 0–5; 0 implies no resistance to Passive Range of Movement (PROM) and 5 indicating joint immobile. On the other hand Angle of catch can be understood via two factors of PROM, the speed of movement and joint angle. The reporting of MTS summarily, involve the quality of muscle and angle of reaction components making it to fit into the body structure and function of the ICF absolutely. It has excellent test retest reliability (ICC = 0.86) in stroke patient [40], with good convergent validity for both elbow and ankle joints (*r* = 0.86 and *r* = 0.62 respectively) [39].
ii. Medical Research Council Manual Muscle Testing (MMT)	

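### The per-domain repeated-measures MANCOVA by default uses only participants with complete data, discarding valid post-intervention results in a trial that expects drop-out

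*Protocol article*

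**What the plan says.** In the protocol article, Data analysis, the group comparisons "will be determined using the general linear model repeated measures, MANCOVA models". The models are specified "for each study domain, adjusted central on baseline as covariates", and the software is SPSS. Univariate comparisons and pairwise tests follow only if the domain model is significant.

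Procedures and Table 1 have the baseline measures repeated after the intervention and at six months. The activity domain holds six instruments, one of which (the Motor Activity Log) yields two scales.

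Under Sample size and power calculation, 56 participants are derived "with 90 % power at α = 0.05". The article then adds: "To incorporate drop-out to follow-up, we hope to recruit a total of 68 participants", which is 17 per group.

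**The concern.** A multivariate general linear model works on a full vector of responses for each person. In SPSS the repeated-measures procedure deletes listwise by default, so one empty cell removes the participant from that domain's model. A missing baseline covariate has the same effect. A participant with a good post-intervention walk test but no 6-month visit contributes nothing to the activity comparison, although walking distance is the outcome on which the trial was sized.

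Two things are at stake. The first is the comparison itself: a set defined by completeness of follow-up is no longer protected by randomisation. The arms differ in session length (60, 90 or 120 minutes). The Background describes stroke survivors as having poor tolerance of activity, and the Objective treats the acceptability of each duration as an open question. Loss that differs by arm is therefore conceivable on the article's own premises, and the Discussion intends a favoured duration to guide clinical recommendations. The second is precision, because the activity domain asks for many scores per person and small gaps accumulate.

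**Working it through.** **Inputs.** From Sample size and power calculation: effect size 0.43, 90 % power, alpha 0.05, four groups, 56 needed, 68 recruited. From Procedures: three assessments. The correlation between repeated measurements is not stated; 0.5 is assumed and a range is shown. The effect size is read as Cohen's f.

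**Reproducing 56.** For the between-groups test in a repeated-measures design with m assessments and correlation ρ:

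λ = f² × N × m / (1 + (m − 1)ρ), with 3 and N − 4 degrees of freedom.

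With f = 0.43, m = 3, ρ = 0.5 and N = 56: λ = 0.1849 × 56 × 3 / 2 = 15.53, and power is 0.905. With equal groups, 56 is the smallest N reaching 90 %. Correlations of 0, 0.25 and 0.75 would give 32, 44 and 68. The article's figure is therefore reproduced under ρ = 0.5.

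**Allowance for loss.** 68 − 56 = 12, or 3 per group; 12/68 = 17.6 %. The article states no drop-out rate, so this is inferred. If exactly 12 participants are lost and the other 56 are complete, power stays at 0.905.

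**Scores needed per person in the activity domain.**
- Upper count: Table 1 gives six instruments, or seven scores if the two Motor Activity Log scales are separate. 7 × 2 post-baseline visits = 14.
- Lower count: the list of dependent variables in Data analysis has about five that belong to activity (functional independence, ADL, functional capacity, gait speed, upper extremity function). 5 × 2 = 10.

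**Illustration.** Assume that, among the 56 retained, each score is missing independently with probability q. Expected complete cases = 56 × (1 − q)^c, where c is the count.

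| q | c = 10 | c = 14 |
|---|---|---|
| 1 % | 56 × 0.99^10 = 50.6 | 56 × 0.99^14 = 48.6 |
| 2 % | 56 × 0.98^10 = 45.8 | 56 × 0.98^14 = 42.2 |
| 3 % | 56 × 0.97^10 = 41.3 | 56 × 0.97^14 = 36.6 |

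**Power at reduced N**, same formula and ρ = 0.5: 0.879 at 52, 0.846 at 48, 0.806 at 44, 0.759 at 40 and 0.702 at 36.

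The rates q are assumptions; the article gives none. Scores taken at one visit tend to be missing together, and clustering of that kind removes fewer people than the table shows.

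**The case against.** The strongest reply is that handling of missing data and the analysis population usually belong in the full protocol or SAP, and neither is shown. The article states no complete-case rule, and multiple imputation before this model would be consistent with every word of it. This stands to the extent that silence on missing data is no finding. It does not remove the point, which concerns the model the article does fix and what that model does with partial data unless something is added.

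Three stronger readings are tempting and are not supported.

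- A reader might infer that the trial has planned a completers' analysis excluding 12 of 68. The allowance is for loss to follow-up, its rate is inferred, and enlarging the sample is routine under any analysis. Those 12 losses also leave the 56 that the power calculation requires.
- A reader might infer that the result will favour the longest sessions because less tolerant participants leave that arm. The article gives no figure for loss by arm. It requires willingness to do the intensive programme, individualises the activities and records attendance separately from outcome assessment. Stopping sessions is not the same as missing an assessment.
- A reader might take the counts of complete cases as forecasts. They depend on assumed rates, independence and a debatable number of scores. If the participation domain is analysed on the single questionnaire's total score, gaps across instruments do not arise there.

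The reply is also right that a mixed model is no complete cure. It assumes data are missing at random and recovers nobody who has no post-baseline value. Used alone, it would also drop the domain-level gate.

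**Conclusion.** The point holds in a limited form. The named procedure, run with SPSS defaults, discards observed post-intervention data from anyone with an incomplete set in a domain, and the article expects drop-out without fixing anything that offsets this.

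The inferred allowance of 12 (17.6 %) preserves about 90 % power if correlation is near 0.5 and the remaining 56 are complete. It does nothing for the randomised comparison. Bias is possible if loss depends on session duration; neither its size nor its direction can be derived from the article.

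Further loss from scattered gaps is illustrative only: about 51 to 41 complete cases with 10 scores, or 49 to 37 with 14, at 1 to 3 % independent missingness. The change is worth making because partial data are lost needlessly and a better method exists in the same software.

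**What to change.** Estimate the between-group differences for each outcome with a linear mixed model for repeated measures (SPSS MIXED). The responses are the post-intervention and 6-month values. The fixed effects are arm, visit, arm by visit and baseline, with an unstructured within-person covariance. Include all participants as randomised who have any post-baseline value.

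Keep the domain MANCOVA as the gate to the univariate comparisons, so that the protection across outcomes is not lost, but run it on multiply imputed data. State in advance how the multivariate test is combined across imputations. Report the complete-case MANCOVA as a sensitivity analysis.

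The cost is revised analysis wording and some additional programming; no new data or software are needed. The price in assumptions is missing at random, which does not cover participants with no post-baseline assessment. Their numbers should be reported by arm so that readers can judge whether loss followed session duration.

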### Objective

The objective of this study is to investigate the relative effectiveness of augmented durations of CCT on the functional capacity of stroke survivors. Additionally, the study will investigate the effectiveness of augmented duration of CCT on upper and lower extremity functions (with respect to body structure/function, activity limitation and participation restriction) post-stroke and the acceptability of the various CCT durations among stroke survivors. For these to be achieved outcomes of interest will be assessed based on the World Health Organisation International Classification of Function, Disability and Health model (WHO-ICF) [36].

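### The sample size is for walking distance alone, but the between-group walking result is reported only behind an activity-domain MANCOVA that the sample size ignores

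*Protocol article*

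**What the plan says.** - **Objective:** the main aim is to "investigate the relative effectiveness of augmented durations of CCT on the functional capacity of stroke survivors". Extremity function by domain, and acceptability, are added as further aims.
- **Sample size and power calculation:** the only calculation is "for a 4-group repeated measure MANOVA in walking distance with 90 % power at α = 0.05". It uses a "between-group difference of 42.5 m (0.43 effect size"), gives 56 in total (14 per group), and is raised to 68 for drop-out.
- **Procedures, Table 1:** the 6MWT is the measure of walking distance. It is listed under activity with the Modified Rankin Scale, Modified Barthel Index, 10-metre walk test (10MWT), Action Research Arm Test and Motor Activity Log. The last has two scores, amount of use and quality of movement.
- **Data analysis:** group differences are assessed by "MANCOVA models (for each study domain, adjusted central on baseline as covariates"). Univariate and least-significant-difference pairwise results follow only if the MANCOVA is significant by Roy's largest root. A multiple regression for each outcome, asking which duration best predicts improvement, stands outside this condition.

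**The concern.** The test that was powered and the test that decides are different. The sample size treats walking distance as a single outcome tested on its own. The analysis rule makes its group comparison conditional on a joint test that also holds two upper-limb scales and two global or daily-living scales. A significant domain result may owe nothing to walking, and with a valid joint test a real walking gain can stay unreported because the other measures did not move. Either way, the 90% in the sample size section is not the probability that the planned analysis yields a walking result.

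**Working it through.** **Inputs.** From the sample size section: 4 groups, effect size 0.43, α = 0.05, 90% power, N = 56. From Procedures: three assessments. Assumed, because the article is silent: 0.43 is Cohen's f, and the correlation between repeated measurements is 0.5.

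**Step 1: the plan's own figure.** For a between-group test over m repeated measurements with correlation ρ, the noncentrality is

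λ = f²·N·m / (1 + (m − 1)ρ), with 3 and N − 4 degrees of freedom.

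With f = 0.43, N = 56, m = 3, ρ = 0.5: λ = 0.1849 × 56 × 3 / 2 = 15.5, and power is 0.905. This reproduces 56. The same formula at N = 68 gives 0.956. No term allows for a multivariate gate.

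**Step 2: outcomes behind the gate.** Six activity tools in Table 1 give p = 6, or p = 7 with both Motor Activity Log scores. With one baseline covariate per outcome, the error degrees of freedom are v = 52 − p, that is 46 or 45. The 6MWT tested alone then has power of about 0.90.

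**Step 3: the gate.** Trials were simulated (20,000 per setting, 40,000 for the null case) with q = 3 hypothesis degrees of freedom, λ = 15.5 on the 6MWT and equal correlation r between outcomes. Two gates at nominal 5% were applied:
- Pillai's trace with its F approximation.
- Roy's largest root θ with its usual F upper bound, F = θ(v − p + q)/p on p and v − p + q degrees of freedom. That is θ × 43/6 on 6 and 43 for six outcomes, and θ × 41/7 on 7 and 41 for seven. It is assumed that this is what the software reports.

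The table gives the probability that the gate and the 6MWT F test are both significant at N = 56 (six outcomes / seven outcomes).

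| Gate and true effect | r = 0 | r = 0.3 | r = 0.5 | r = 0.7 |
|---|---|---|---|---|
| Pillai, only 6MWT shifts | 0.46 / 0.40 | 0.57 / 0.52 | 0.70 / 0.66 | 0.87 / 0.84 |
| Pillai, 10MWT shifts equally | 0.77 / 0.72 | 0.80 / 0.77 | 0.87 / 0.85 | 0.90 / 0.90 |
| Pillai, all shift equally | 0.90 / 0.90 | 0.83 / 0.80 | 0.72 / 0.67 | 0.60 / 0.54 |
| Roy with F bound, only 6MWT shifts | 0.87 / 0.85 | 0.89 / 0.89 | 0.90 / 0.90 | 0.90 / 0.90 |

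**Step 4: size of the gate.** With no effect on any outcome, Pillai's gate is significant in about 4 to 5% of trials and Roy's with the F bound in about 35 to 36%.

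**Step 5: full recruitment.** If all 68 are analysed and only the 6MWT shifts, the Pillai-gated power is 0.61 / 0.56 at r = 0 and 0.86 / 0.83 at r = 0.5, against about 0.955 ungated.

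**The case against.** - **The plan names Roy's root, not Pillai's trace.** This stands. Under the usual F bound a walking gain is seldom blocked. The reason is that the gate opens in about a third of null trials, so it hardly serves as protection before several univariate tests and unadjusted pairwise comparisons. The 6MWT F test keeps its own 5% level in either case.
- **An effect on the 6MWT alone is unlikely.** Gait speed sits in the same domain, the circuit gives equal work to arms and legs, and the Background cites benefit for gait and upper limb. This stands in part: the loss shrinks when gait speed responds too. But the Discussion itself expects arm and leg to differ in response, and the table shows that a shared response does not always rescue power.
- **The regression is ungated.** This is true, so walking distance is not wholly behind the gate. But that analysis asks which duration predicts improvement. It is not the four-arm comparison with control that was powered.
- **The mapping is inferred.** The Data analysis section lists constructs rather than scales. Reading functional capacity as the 6MWT, and counting six or seven outcomes, are inferences from Table 1. That walking distance is the powered outcome is stated outright.
- **Domain tests serve a stated aim,** namely to see which domain responds most. They can do so as secondary analyses.

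A reader might infer that the gate halves the power of the main question. The documents do not support that as a general statement. It needs a valid criterion in place of the one named, an effect confined to the 6MWT, and low correlations.

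**Conclusion.** The mismatch holds: the trial is sized on one outcome whose between-group result is conditional on a six- or seven-outcome test, and the sample size makes no allowance for it.

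The consequence depends on the criterion:
- **As written (Roy, usual F bound):** almost no power is lost, and the gate gives almost no protection.
- **With a valid gate:** power for walking distance ranges from about 0.4 to almost the full 0.90. The fall to about half is the unfavourable end.

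These figures rest on f = 0.43, three measurements, repeated-measures correlation 0.5 and equal correlation between outcomes. The structural point needs none of them.

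**What to change.** 1. Name 6MWT distance as the single primary outcome, at one prespecified visit. Post-intervention is an example; the article does not fix a primary visit, so the sponsor must choose.
2. Test it directly at 5% by a four-arm ANCOVA on baseline 6MWT, outside any MANCOVA gate.
3. Keep the domain MANCOVAs as secondary analyses.
4. Restate the power for this test. At a single visit λ = 0.1849 × 56 = 10.4, so power is about 0.74 if baseline explains nothing. If baseline explains half the variance (an assumption), λ = 10.4/0.5, about 20.7, which exceeds the 15.5 that gives 0.905.

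**Cost:** a short wording change and no new data. The other activity outcomes become explicitly secondary. The activity-domain test loses a walking measure if the 6MWT is taken out of it, but the 6MWT may stay in that test as a secondary analysis.

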	Participants’ gait speed will be measured using 10MWT [48], which will be calculated by the time required to cover a distance of 10 m. Participants will be asked to walk at their maximal speed using their regular foot wear and walking aids (for those who use aids). The test will be performed on a 14 m walkway, to avoid the effects of acceleration and deceleration, therefore the individual may accelerate 2 m before entering the 10 m distance and 2 m to decelerate afterward, this will ensure a steady velocity within the 10 m mark. 10MWT shows a high intra-observer reliability (ICC = 0.95) and validity (*r* = 0.79) in stroke survivors [49].
v. Action Research Arm Test (ARAT)	
	The ARAT is a criterion-rated assessment of upper extremity activity limitations [50]. The ARAT includes 19 items divided into four subscales: grasp, grip, pinch, and gross movement. The items within each subtest are ranked based on a four-point ordinal scale ranging from zero to three, where three symbolises normal performance on each item. The items are ordered in a hierarchy, allowing skipping some items if the person is unable to do an earlier item normally. A score of 57 indicates normal performance. The test has a good test-retest reliability for both chronic and acute stroke, ICC = 0.963 [51], internal consistency α = 0.985 [50] and construct validity in relation to the arm section of Fugl Meyer, ICC = 0.925 [51].
vi. Motor Activity Log (MAL)	
	The motor activity log (MAL) is a rating scale that evaluates how the affected hand is used to perform 30 daily activities (e.g., feeding, turning a door handle). For each activity, the patient rates how much the affected hand is used (amount of use, AOU) and how well the activity is performed (quality of movement, QOM). Ratings are usually on a scale of 0 to 5, with higher scores representing better functions. Scores on each scale are calculated as the mean of the scored items attempted with the affected arm. Its internal consistency is good, α > 0.81, with acceptable test retest reliability *r* > 0.91 and stability ratio >3 for the QOM and AOU, though not found to be reliable [52].
Participation assessment	
Stroke specific Quality of Life Questionnaire (SS-QOL)	

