	SS-QOL is selected to assess community participation. The SS-QOL is a self-report questionnaire consisting of 49 items cutting across 12 domains of mobility, energy, upper extremity (UE) function, work/productivity, mood, self-care, social roles, family roles, vision, language, thinking, and personality specific for stroke survivors. The domains are graded individually, and a total grade is also rendered [53]. SS-QOL has a good content validity, kappa coefficient ranged from 0.75-1.00, it demonstrated multiple representations of the ICF categories and covered a broad range of the ICF components that were meaningful for the stroke subjects [54].
Acceptability	
	To assess acceptability participants will complete a purpose-designed questionnaire [55]. The tool is a six-item scale adapted from the original treatment acceptability questionnaire, it is a seven point scale, with lower score indicating lower acceptability. Possible score on the scale ranged from 6–42. Participants in all the intervention groups and the control will be asked to provide information specific to their treatment. The test has not been tested for reliability and validity.

All baseline measures will be repeated immediately post-intervention and 6 months follow-up, excluding descriptive personal and stroke data. Also at this time, the intervention acceptability measure will also be applied.

Participant adherence will be duly monitored and recorded for each session in terms of attendance (number of sessions) and amount of practice (within sessions – time spent and repetitions where relevant). Fidelity of the intervention will be monitored by the primary investigator performing video recordings of randomly chosen sessions in each arm. Co-investigators will review these videos for compliance with the established practice protocols. Safety issues and adverse events will be recorded by treating staff in each group and monitored by the co-investigators. Previous trials using CCT have found no increase in adverse events as compared to usual care [32].

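### Roy's largest root, with the p-value SPSS prints by default, is not a 5 % gate: under the null it opens in about 16 % of trials with two scores and 33-37 % in the activity domain

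*Protocol article*

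**What the plan says.** All of the relevant text is in the protocol article.

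- **Software** (Data analysis): "Data will be recorded in Microsoft Excel before being exported to Statistical Package for Social Science (SPSS").
- **Models** (Data analysis): general linear model repeated measures, "MANCOVA models (for each study domain, adjusted central on baseline as covariates"). There is therefore one multivariate test per ICF domain, not one for the whole trial.
- **Dependent variables** (Data analysis): "spasticity, muscle strength, functional independence, ADL, functional capacity, gait speed, upper extremity function and impairment". The list does not say how many scores enter each domain's model.
- **Gate** (Data analysis): "If the MANCOVA is found to be significant (Roy’s largest root), univariate between-groups results will be reported". Pairwise post hoc tests by least significant difference (LSD) follow from the same condition.
- **Arms** (Participants): eligible patients "will be randomised into one of four arms of the study".
- **Scores** (Procedures, Table 1): two body-function tools (MTS, MMT), six activity tools (MRS, MBI, 6MWT, 10MWT, ARAT, MAL) and one participation tool (SS-QOL). Some tools give more than one score. The MAL rates "how much the affected hand is used (amount of use, AOU) and how well the activity is performed (quality of movement, QOM"), and for the SS-QOL "The domains are graded individually, and a total grade is also rendered".

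No other multivariate criterion and no other multiplicity control is named.

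**The concern.** The multivariate test is the only stated barrier between a trial with no effect and a set of unadjusted univariate and LSD results. It works as a barrier only if it rejects in about 5 % of null trials.

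Roy's statistic is the largest eigenvalue of E⁻¹H, where H and E are the hypothesis and error matrices. Its default F approximation treats that maximum as if it were a single ratio fixed in advance. The approximation is exact with one outcome or one hypothesis degree of freedom. With four arms (three hypothesis degrees of freedom) and two or more outcomes, the F is an upper bound and the p-value a lower bound, so the gate opens too often.

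The activity domain matters most. It contains the six-minute walk test, and walking distance is what the sample size is built on. The Discussion says that a duration supported by the results will guide clinical recommendations, and pairwise contrasts between durations are what would supply that support.

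**Working it through.** **Inputs**

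- Groups: 4, so hypothesis df q = 3 (Participants).
- N: 56 evaluable, 68 recruited (Sample size and power calculation). The 56 reproduces: with f = 0.43, three measurements and an assumed correlation of 0.5 between them, λ = 0.43² × 56 × 3 / (1 + 2 × 0.5) = 15.5 on 3 and 52 df, which gives power 0.905. The sample size is not at issue; it only supplies N.
- α = 0.05 (same section).
- Scores per domain, p: 1 for the SS-QOL total, 2 for body function, 6 for activity by tools, or 7 if both MAL scores enter. These are counts from Table 1; the analysis section does not fix them.
- Covariates: one baseline value per score (assumed), so error df ve = N − 4 − p.
- Normal data and the default SPSS p-value (both assumed).

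**Formula**

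With r = max(p, q), F = root × (ve − r + q) / r, referred to r and ve − r + q df. Example for p = 6, N = 68: ve = 68 − 4 − 6 = 58, r = 6, df = 6 and 58 − 6 + 3 = 55. The 5 % point applied is F = 2.27. The simulated true 5 % point of this statistic is about 3.71.

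**Gate opening under the complete null** (40,000 simulated trials per case)

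| Scores in model | Roy, N = 56 | Roy, N = 68 | Pillai, N = 56 / 68 |
|---|---|---|---|
| 1 | 4.9 % | 4.9 % | 4.9 % / 4.9 % |
| 2 | 16.4 % | 16.4 % | 4.7 % / 4.9 % |
| 6 | 35.2 % | 34.9 % | 4.4 % / 4.4 % |
| 7 | 36.6 % | 36.1 % | 4.5 % / 4.7 % |

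The first row recovers the nominal 5 %, as it should, because the approximation is exact for one score. Wilks' lambda on the same draws gave 4.8-5.2 %. Simulations of individual patient data with baseline covariates, run separately, gave 33-36 % for six or seven scores, so 33-37 % covers all runs. Recruiting 68 instead of 56 makes no material difference.

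**From an open gate to a false result** (data-level simulation, null, activity domain with 6-7 scores)

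- Gate open and at least one univariate p < 0.05: about 21-22 % with uncorrelated outcomes, 16-18 % at correlation 0.5, and 11 % at correlation 0.8.
- Gate open and at least one LSD p < 0.05: about 30 % at correlation 0.5, against 4-5 % when Pillai's trace is the gate. As written, the LSD step depends on the MANCOVA and not on a significant univariate test, so this figure follows the text.
- For two scores, gate open with a false univariate result: about 8-10 %.

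**The case against.** **The p-value method is inferred.** The article names SPSS and Roy's root but not how significance is obtained. Roy's criterion with correct critical values is a valid 5 % test; the fault lies in the default approximation. This stands as a condition on the finding. It does not remove it, because the text provides for nothing other than the software's output.

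**One figure for every gate.** A reader might infer that all univariate results sit behind a gate with a 36 % error rate. The article does not support that. It sets one model per domain and leaves the number of scores open, so the rate is 5 % for a single participation score and about 16 % for two body-function scores. Only the activity domain reaches a third or more. Entering the twelve SS-QOL domains separately would give a rate in the high thirties, but that is hypothetical: the list of dependent variables names no quality-of-life measure, and the tool also yields a total.

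**An open gate is not yet a false finding.** This is correct. The omnibus univariate error is one third to two thirds of the gate-opening rate in the activity domain, and the correlation that determines it is not in the documents. It remains two to four times the nominal 5 %, and the LSD error is higher.

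**Non-normality.** It is tempting to add that the short ordinal scales make Roy's root worse still. All calculations used normal data, so no such claim is made.

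**Conclusion.** The rule as written does not deliver the error rate that its threshold implies. If the default SPSS p-value is used, the gate is sound for one score, about three times too liberal for two (16 / 5), and about seven times too liberal in the activity domain (33-37 % against 5 %). The results that then reach the report contain at least one false univariate difference in about 11-22 % of null trials in that domain, and at least one false LSD pair in about 30 % at correlation 0.5.

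These figures rest on Table 1 counts for the number of scores, one baseline covariate per score, normal data, 56 to 68 participants and the complete null. The direction of the error does not depend on the exact count, provided that at least two scores enter the model. It should be corrected before analysis, because the criterion is fixed in the text and the domain worst affected holds the powered outcome.

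**What to change.** In Data analysis, replace Roy's largest root with Pillai's trace as the single pre-stated criterion for every domain. SPSS prints it in the same table. Wilks' lambda, or an exact or simulated p-value for Roy's root, would also repair the gate. State at the same time which scores enter each domain's model, since the article leaves this open.

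The change is two words. It needs no extra patients, visits or measurements; fewer domains will pass by chance.

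The change restores a 5 % gate within each domain when nothing differs between arms. It does not adjust across domains: three correct gates would still give 1 − 0.95³ = 14 % for at least one false opening if they were independent. Nor does it control the univariate and LSD tests once a gate has opened on a real effect. Those need their own decision.
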